### Who will take informed consent {26a}

Before proceeding with any examination related to the research, the investigator will obtain the patient’s freely given FASCE informed consent, in writing.

### Model consent form and other related documentation given to participants and authorized surrogates {32}

The Supplementary Material file contains the French informed consent form that the patient signs prior to their inclusion in the trial (version 2, updated 1 July 2017).

### Additional consent provisions for collection and use of participant data and biological specimens {26b}

Biological samples for bacterial strain identification will be collected and stored if the patient has signed the biocollection informed consent form. In this informed consent form it is noted that the samples may be used for other pieces of scientific research. This biocollection and consent procedure has been registered under number DC-2011-1399 by the French Ethics Committee: CPP Ouest IV.

## Interventions

### Explanation for the choice of comparators {6b}

As already stated, although acne is not an infectious disease, oral antibiotics have remained a mainstay of treatment over the last 40 years. The anti-inflammatory properties of oral antibiotics, particularly cyclines, are effective in treating inflammatory acne [39, 40].

All the guidelines - French [41], European [42] and American [43] - recommend cycline for first-line treatment but limited to a treatment period of 3 months to minimize the development of bacterial resistance. This is why the treatment duration of the comparator arm we chose is doxycycline 100 mg/day for 3 months. The guidelines specify also that monotherapy with a systemic antibiotic is not recommended. Concomitant topical therapy with, for example, benzoyl peroxide should be used with systemic antibiotics and for maintenance after completion of systemic antibiotic therapy. Patients in the two study arms will receive this topical therapy.

The primary objective is the efficacy of doxycycline or spironolactone seen at M4 and/or M6. To avoid results bias and because our experience shows that maximum efficacy is seen for cycline between M4 and M6, the best clinical response between M4 and M6 will be chosen for the primary endpoint.

The response of acne to spironolactone may not be optimal after only 3 months of treatment [22]. A retrospective trial reported by Burcke and Cunliffe showed an average reduction in acne that was optimal at month 6 [24].

In conclusion, in order not to bias the study in either direction, regarding the primary objective, the efficacy of the two treatments will be measured at 4 and 6 months in each arm and the best results in the two arms will be compared (Fig. 1). At the end of the M6 visit, after the clinical evaluation, all the data will be accessible and open to the patient and the investigator. Patients with complete or partial remission will continue the trial. Other patients will drop out of the trial and be treated by the investigators according to their usual practice. The same approach will be used at the M9 visit: relapse patients will drop out of the trial and will be treated by the investigators according to their usual practice.

**Fig. 1 Fig1:**
[figure not shown]
Study diagram

### Intervention description {11a}

As this is a double-blind study, the intervention drug, its comparator and the placebo will be managed by the pharmacist of the coordinating centre, CHU Nantes. The oral dose of 150 mg of spironolactone, once a day during the complete trial period has been chosen based on the literature and our own experience. Pills will be dispensed at each protocol visit (i.e. every 2 months for 12 months). The efficacy of spironolactone has been established by several studies that showed improvement, with reductions in lesions ranging from 50 to 100% in women treated for acne [44]. In most of these studies, the dosage range used was 100–200 mg daily, with response noted over approximately 3 months [44].

For the comparator, as recommended by the French Guidelines for acne treatment [41], the doxycycline treatment for acne vulgaris will be 100 mg administered once a day for 3 months. From M4 to M6, a placebo will be administered. Pills will be dispensed at each protocol visit (i.e. every 2 months for 6 months). The two treatments will be taken orally. As the antibiotics must be taken during a meal, and to retain the double-blind effect of our trial, the patients in the two arms should take their treatment during a meal. The treatment should be taken with a full glass of water and the patient should remain in the upright position for at least 1 h.

Monotherapy with a systemic antibiotic is not recommended [43]. Concomitant topical therapy with, for example, benzoyl peroxide 5%, should be used with systemic antibiotics and for maintenance after completion of systemic antibiotic therapy. Patients in the two arms will receive this topical therapy.

The treatment continues after M6, which is the main objective to meet the secondary objectives. However, from the M6 visit, the treatment will be stopped in the event of failure to respond, the patient will be withdrawn from the study and the investigator will prescribe another treatment according to usual practice. In the case of treatment success, the patient in the spironolactone arm will continue with this treatment “open”, and the patient in the doxycycline arm will continue to participate only with the topical therapy*.* The schedule for the complete trial is shown in Fig. 2.

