### Strategies to improve adherence to interventions {11c}

Compliance will be assessed in the FASCE trial by return tablet count. At the M2, M4, M6, M9 and M12 visits, the patient will return the empty study drug packages and the investigator or a member of their team will count them.

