### Plan to promote participant retention and complete {18b}

The patient will be given a diary at the randomization visit, to note their health resource consumption, medical compliance, concomitant treatments and AEs. The visits will be arranged every 2 months up to M6, where the main objective is set. Empty blisters will be collected and counted at each visit. At each visit, the drugs prescribed will be for 2 months (blinded allocation of spironolactone/doxycycline and a placebo plus concomitant topical therapy). At visit M2 (2 months after randomization), the physician or a member of their team will have to be vigilant and tell the patient to carefully follow the chronological order of treatments. Two envelopes will be given to the patient, one for M3 (blinded allocation of spironolactone or doxycycline) and one for M4 (blinded allocation spironolactone or a placebo in place of doxycycline). As aforementioned, the guidelines stipulate that treatment with doxycycline should not exceed 3 months. For this reason, patients in the doxycycline arm will be given a placebo during month 4 and the following months [41–43].

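### The M6 continuation rule is stated in two different terms and placed just after the code is opened, and the two-monthly dispensing statement does not fit the M9 and M12 visits

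*Protocol article*

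**What the plan says.** **Continuation at M6.** The protocol article, section {6b} (choice of comparators), states "Patients with complete or partial remission will continue the trial"; all other women leave and are treated according to usual practice. Section {11a} (intervention description) stops treatment and withdraws the woman if she fails to respond, and adds: "In the case of treatment success, the patient in the spironolactone arm will continue with this treatment". Section {20c} (non-adherence and missing data) has a third statement: assigned treatment continues until one of a list of events, which includes neither non-response nor relapse.

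**Opening of the code.** Section {6b} says that at the close of the M6 visit, once the clinical evaluation is done, "all the data will be accessible and open to the patient and the investigator". The continuation rule is the next sentence. Sections {8} and {17a} confirm that blinding is lifted only after the primary endpoint has been measured.

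**Dispensing.** For spironolactone, section {11a} states "Pills will be dispensed at each protocol visit (i.e. every 2 months for 12 months". For the comparator it states "Pills will be dispensed at each protocol visit (i.e. every 2 months for 6 months". Section {11c} gives the visit calendar: "At the M2, M4, M6, M9 and M12 visits, the patient will return the empty study drug packages". Section {18b} limits the two-monthly rhythm: "The visits will be arranged every 2 months up to M6, where the main objective is set".

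**The concern.** Sections {8} and {17a} give months 6-12 the purpose of assessing whether efficacy is maintained, and section {7} plans between-arm comparisons at 9 and 12 months. Those comparisons depend on who is kept at M6. If the criterion can be read in two ways, centres may keep different women. If the decision is made once the allocation is visible, a borderline woman may be kept more readily in one arm than in the other.

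The dispensing wording matters for the same period. After M6 only the spironolactone arm takes study drug, so any uncertainty about supply falls on one arm.

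**Working it through.** **1. Continuation: the two wordings side by side.**

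| Section | Stays after M6 | Leaves |
|---|---|---|
| {6b} | complete or partial remission | everyone else |
| {11a} | treatment success | failure to respond |
| {20c} | everyone, until a listed event | non-response and relapse are not listed |

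The only explicit success rule is in section {12}. It requires both a fall of at least two grades in AFAST score 1 (or to 0 from a baseline of 1) and a fall of AFAST score 2 to grade 1 (or to 0 from a baseline of 1). The best response between M4 and M6 counts. Two types of patient show the difference:

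- *Partial response.* AFAST score 1 falls from 3 to 2, a change of 3 - 2 = 1 grade. One is less than two, so this is not a success under {12}. It could be a partial remission under {6b}, so she stays. Under {11a} she is not a success by the {12} rule, yet has arguably not failed to respond, so her status is open.
- *Success at M4, lost by M6.* Under the best-response rule of {12} she is a success. Judged on her state at M6, she may not be in remission under {6b}.

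The ambiguity carries forward. Section {6b} removes relapsing women at M9, but the relapse definition in {12} applies only to women who had been a success. A woman kept in partial remission has no defined relapse.

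**2. Order of events at M6.** Section {6b} gives: clinical evaluation, then code opened, then the statement of who continues. The scores are therefore obtained blind. Nothing in the text says that the continuation decision is recorded before the code is opened.

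**3. Route to the results.** Section {20c} collects no further data, apart from safety data, on a woman released from the study, and withdraws patients with missing data from the clinical secondary analyses. A woman released at M6 thus has no M9 or M12 efficacy data. The continuation decision is in effect the inclusion rule for those comparisons.

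**4. Size.** The document does not give the share of women in partial remission without success. Its planning rates (section {14}: 70% and 50% success) with about 200/2 = 100 women per arm give 0.70 x 100 = 70 and 0.50 x 100 = 50 successes. These are only a rough guide to the numbers continuing if success alone decides, because they refer to the best of M4 and M6, not to status at M6. If partial remission also qualifies, both numbers rise by an unknown amount.

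**5. Dispensing calendar.**

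- Two-monthly over 12 months: months 0, 2, 4, 6, 8, 10, which is six occasions.
- Protocol visits before M12: months 0, 2, 4, 6, 9, which is five occasions.
- Visit intervals: 2, 2, 2, 3, 3 months (sum 12).

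M8 and M10 are not visits, and M9 is not on a two-monthly cycle. The two halves of the {11a} statement cannot both hold after M6. The comparator statement, which covers six months only, fits the calendar.

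**The case against.** **The continuation wordings may be compatible.** Section {11a} withdraws only women who fail to respond. A woman in partial remission has responded, so on an ordinary reading she stays under both sections, and {11a} does not say that its treatment success is the {12} endpoint. The full protocol may also define partial remission, and its absence from a condensed article is no fault in itself. This has weight, but it settles the matter only by choosing a meaning that the text does not state. {11a} names success as the condition for continuing on spironolactone, and the only success rule printed is that of {12}.

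**The M6 assessment is blind.** This stands. A reader might infer that opening the code at M6 compromises the primary endpoint. The documents do not support that: evaluation and endpoint measurement both come first. What remains is the continue/stop judgement, whose place relative to code opening is not fixed.

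**A supply gap.** A reader might multiply five dispensing visits by two months, obtain 10 months of drug for a 12-month course, and conclude that 2 of the 6 open months (33%) are uncovered. The documents do not show this. The statement "At each visit, the drugs prescribed will be for 2 months" in {18b} is followed by a parenthesis describing the blinded supply, and the other two-month quantity, in {16c}, is the day 0 prescription. No section gives a pack size at M6 or M9. Sections {8} and {11a} describe continuous treatment, and {11a} refers to Fig. 2 for the schedule, which was not available for this review.

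**The later phase is declared open-label and response-selected.** This is true, and it limits the importance of the point. It does not remove the need for a single selection rule.

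**Conclusion.** The point holds at minor severity. The M6 continuation criterion is given in terms that can class the same woman differently, and it is stated at code opening with no requirement to record the decision first. Because of the data rules in {20c}, the decision determines the groups compared at M9 and M12.

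The effect is confined to the M9 and M12 secondary outcomes. The primary endpoint at M4/M6 and the 6-month cost-effectiveness analysis are untouched. No size can be computed: any figure for the number of women affected would rest on an assumed share of partial responders, for which the document gives no basis. That the decision would differ by arm is a possibility that the text leaves open, not something it demonstrates.

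The dispensing statement is inconsistent with the visit calendar after M6. This is a wording conflict and does not show interrupted treatment.

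The conclusion assumes that {20c} applies to women who leave at M6 under {6b} or {11a}, and that success in {11a} may be read as the {12} rule.

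**What to change.** 1. The clinical team should reconcile sections {6b}, {11a} and {20c} on who continues after M6, and sections {11a}, {11c} and {18b} on dispensing after M6. No continuation criterion or dispensing interval is proposed here.
2. The M6 AFAST scores and the continue/stop decision should be entered and locked in the eCRF before the allocation is displayed. This keeps the evaluation order that {6b} already sets and extends it to the decision.

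The cost is protocol wording, one sequence check in the eCRF and a few minutes at the M6 visit. The sample size and the primary analysis do not change.

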**Fig. 2 Fig2:**
[figure not shown]
Study schedule. AFAST, Adult Female Acne Scoring Tool; EQ-5D, Euroqol-5 dimensions; CADI, Cardiff Acne Disability Index; D, day; M, month

### Criteria for discontinuing or modifying allocated interventions {11b}

No dosage adjustment is required by the protocol. However, in case of hyperkalaemia, the spironolactone treatment will be adjusted. The patient must stop using the product and seek emergency medical attention immediately if she develops signs and symptoms of a serious hypersensitivity reaction such as throat tightness, difficulty breathing, feeling faint or swelling of the eyes, face, lips or tongue. Also, she must stop using the product if she develops hives or itching of the face or body.

### Strategies to improve adherence to interventions {11c}

Compliance will be assessed in the FASCE trial by return tablet count. At the M2, M4, M6, M9 and M12 visits, the patient will return the empty study drug packages and the investigator or a member of their team will count them.

### Relevant concomitant care permitted or prohibited during the trial {11d}

Due to spironolactone, anything that can induce hyperkalaemia is forbidden: potassium-sparing diuretics, potassium supplements and drugs such as ACE inhibitors, angiotensin II antagonists, non-steroidal anti-inflammatory drugs (NSAIDs), heparin and low molecular weight heparin, ciclosporin, tacrolimus and trimethoprim. Lithium is also not recommended in this trial. Concurrent use of lithium and spironolactone may result in increased lithium concentrations and lithium toxicity due to decreased lithium excretion. So, the monitoring of lithium plasmatic concentration will be reinforced.

### Provisions for post-trial care {30}

At the end of the clinical research, the patient will be followed by her dermatologist and will benefit from the usual care of her disease. The Sponsor will take out an insurance policy covering the financial consequences of its civil liability in compliance with the regulations.

### Outcomes {12}

The primary endpoint corresponding to the treatment efficacy is determined by the probability of success in each arm. In order to reduce the variability related to the fluctuation over time of the therapeutic response, we took the maximum value of this response. This maximum value appears between the fourth and sixth month of treatment. We could also have taken the average measured over 2 months, but clinically this is not interesting because the optimal time of efficacy is different between the two treatments This probability of success (or relapse) is defined by a decrease in both AFAST scores: (1) AFAST score 1 (corresponding to the GEA score): decrease of at least two grades compared to baseline or to grade 0 if the baseline was at 1, and (2) AFAST score 2 (mandibular score): decrease to grade 1 if baseline was > 1 or to grade 0 if the baseline was at 1.

AFAST score 1 (also called GEA) assesses the comedones (open and closed), the non-inflammatory lesions, the papules and pustules and the nodules. The stage is defined according to a global evaluation of severity of acne and ranges from grade 0 (no acne) to grade 5 (the worst situation). AFAST score 2 assesses acne on an area from the left and right mandibular zone to the upper edge of the trunk and ranges from grade 0 (no acne) to grade 3 (the worst situation).

For the secondary endpoints:
Safety/tolerance: reporting of the number and type of adverse events (AEs) and serious adverse events (SAEs) up to month 12 of follow up and abnormal values of ionogram (sodium, potassium, chlorine and calcium) at 0, 2, 4 and 9 months. First the percentage of AEs and SAEs will be calculated then they will be classified according to the organ affected.Efficacy: these outcomes correspond to the reporting of the:
Number of patients with AFAST score 1 (GEA) at 0 or 1, at M2, M4, M6, M9 and M12Number of patients with AFAST score 2 (mandibular) at 0 or 1, at M2, M4, M6, M9 and M12Number of patients with both AFAST scores 1 and 2 at 0 or 1, at M2, M4, M6, M9 and M12Number of inflammatory lesions of the face at D0 (baseline), M2, M4, M6, M9 and M12Number of retentional lesions of the face at D0, M2, M4, M6, M9 and M12Number of face lesions at D0, M2, M4, M6, M9 and M12Number of trunk lesions (factor F2 of ECLA) at D0, M2, M4, M6, M9 and M12Number of patients with relapses at M4 and M6

The definition of relapse is the same as the primary endpoint:
AFAST score 1 (GEA score): increase of 2 points in the score at the previous visit, in the case of success, orAFAST score 2 (mandibular score): increase of 1 point in the score at the previous visit, in the case of success
Number of patients with reappearance of 10% or more of inflammatory lesions at M6

For these nine outcomes, percentages will be calculated at each time point:
Quality of life (QoL): reporting of the scores of two QoL questionnaires: the Euroqol-5 dimensions (EQ-5D) and the Cardiff Acne Disability Index (CADI) at M2, M4, M6, M9 and M12. This outcome will be measured by the percentage of patients whose quality of life has improved relative to baseline.Microflora: bacterial and parasitic sampling at D0 and M4. The presence *of P. acnes, M. Furfur* and *S. epidermidis/ aureus* will be sought and a change in these populations from baseline will be measured at M4. A percentage of decrease will be calculated.Medico-economy: incremental cost-effectiveness ratio (cost per quality-adjusted life year (QALY)) of the comparison between spironolactone and cycline at 6 months. Criteria for the calculation of the cost-effectiveness ratio are detailed in “Methods for additional analyses”.

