## Introduction

### Background and rationale{6a}

To understand exactly what acne vulgaris is, we must begin below the skin’s surface, deep in the hair follicle. The follicle, which is lined with skin cells, contains sebaceous glands that produce oil (sebum). Normally the skin cells that line the follicle are shed and brought to the skin’s surface by the sebum and are then washed away. However, when the cells stick together instead of shedding, they form a plug or blockage. A clogged pore is a commonly used term for a plugged follicle. Beneath the plug, a sac is formed (known as a microcomedone) that contains dead skin cells and oil. Bacteria (*Cutibacterium acnes*) grow freely in this environment, feeding on the dead skin cells and oil. As the sac continues to grow, either a whitehead (known as a closed comedone), or a blackhead (open comedone) forms. In more serious cases, the sac will become larger, encouraged by the cells that the body sends into the sac to fight the infection. Inflammation will result, and a bump (papule or pustule), painful nodule or cyst will develop.

Though acne becomes less common in adulthood than in adolescence, nearly half of people in their twenties and thirties continue to have it. About 4% continue to have difficulties into their forties [1].

Acne vulgaris has increased in women over the past 10 years. The prevalence is currently 15–50% across different studies [2–4]. Acne in women is now a well-known entity considered as different to adolescent acne [5, 6]. It is reported to most often affect women aged 25 years or older. A recent study isolated two distinct types of clinical presentation: (1) the first is similar to teenager acne, with diffuse acne lesions over the face including hyperseborrhea, retentional lesions (mainly closed comedone) and superficial inflammatory lesions and (2) the second is always mild-to-moderate acne located on the inferior third of the face (mandibular location), mainly with few deep, inflammatory chronic cysts [7].

The physiopathology of adult female acne is characterized mainly by two specific factors:

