### Eligibility criteria {10}

It is commonly acknowledged that acne affecting female patients under 20 years of age is considered to be “adolescent female acne”. Since this protocol concerns adult female acne, the recruited patients will be women aged at least 20 years. These patients will have acne vulgaris with at least 10 inflammatory lesions and no more than 3 nodules. The eligibility criteria are shown in Table 1.

**Table 1 Tab1:** Inclusion and non-inclusion criteria of the FASCE trial

Inclusion criteria	Non-inclusion criteria
• Female patient ≥ 20 years old	• Patient affected by active/progressive diseases, as infections including hidradenitis suppurativa, cancers or endocrine syndrome (e.g. polycystic ovary syndrome)*,* Addison’s disease)
• Patient with acne, with at least 10 inflammatory lesions and no more than 3 nodules (GEA score between 2 and 4)	• Patient affected by rosacea (folliculitis)
• Patient who already had one cycline course for her acne treatment with a 3-month* wash out or who never took any cyclines	• Patient with contra-indication to the use of one of the investigational products or auxiliary: ◦ Patient with intolerance or hypersensitivity to cyclines, spironolactone or to any ingredient present in associated benzoyl peroxide gel ◦ Patient with significant impairment of renal excretory function, acute or chronic renal failure, anuria ◦ Patient with life-threatening or very severe hepatic impairment. (grade III or IV)
• Patient having signed an informed consent	• Patient with hyperkalaemia or strongly requiring potassium-sparing diuretics (e.g. amiloride, canrenoate, eplerenone, triamterene) or treated continuously with ACE inhibitors, angiotensin II antagonist, NSAIDs, heparin and molecular-weight heparin, ciclosporin and tacrolimus, or treated with lithium
• Absence of use of oral antibiotics and zinc salts in the last 30 days	• Patient requiring topical isotretinoin or who stopped this drug less than 2 weeks ago
• Absence of use of topical antibiotics in the last 15 days	• Association with potassium salts except in the case of hypokalaemia
• Absence of use of systemic isotretinoin and antiandrogens in the last 6 months (but antiandrogens used as contraceptive are authorized)	• Patient previously treated with spironolactone
• Absence of microphysiotherapy in the last 15 days	• Pregnant woman or likely to become pregnant or nursing and refusing to use an effective contraceptive method

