## Data collection and management

### Plans for the assessment and collection of outcomes - description of the parameters for evaluating efficacy {18a}

The first endpoint is the new validated score for adult female acne: the Adult Female Acne Scoring Tool (AFAST) [36]. The AFAST uses two independent scores: score 1 corresponding to GEA grading for acne on the face [34] and score 2 corresponding to the evaluation of the mandibular region. Scores are not added together. For each patient, AFAST score 1 (GEA) and AFAST score 2 should be assessed by the same evaluator at each visit.

The other score we will use is the ECLA. The ECLA chart for evaluation of acne has been developed by six dermatologists (in private and hospital practice) [35]. It is composed of 3 factors: factor 1 (F1) counts the acne lesions on the face, factor 2 (F2) counts the acne lesions on the trunk and factor 3 (F3) counts the scars. In this study, only factor F2 will be used. Factor F2 assesses the extensive character of acne lesions in five defined areas: cervical area (F2N), chest area (F2C), back area (F2B) and arm area (F2A) according to a qualitative scale where 0 = absent, 1 = poor, 2 = medium and 3 = significant. It is completed by counting the nodules present in each area.

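### As written, the primary success rule gives an eligible woman with mandibular grade 0 at baseline no way to succeed, whatever happens on her face

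*Protocol article*

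**What the plan says.** The protocol article, Outcomes {12}, builds the primary endpoint from two components that must both be met: "This probability of success (or relapse) is defined by a decrease in both AFAST scores".

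- Score 1 (the GEA, whole face): "decrease of at least two grades compared to baseline or to grade 0 if the baseline was at 1".
- Score 2 (mandibular zone): "decrease to grade 1 if baseline was > 1 or to grade 0 if the baseline was at 1".

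The same section states that score 2 "ranges from grade 0 (no acne) to grade 3 (the worst situation".

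In Eligibility criteria {10}, Table 1, the only severity requirement is "Patient with acne, with at least 10 inflammatory lesions and no more than 3 nodules (GEA score between 2 and 4"; no mandibular grade is mentioned. The section on assessment and collection of outcomes {18a} adds: "The AFAST uses two independent scores".

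Under Statistical methods {20a}, the modified intention-to-treat set removes only randomized women who turn out not to meet the inclusion criteria and those who never start treatment.

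**The concern.** The mandibular component has a branch for baselines above 1 and a branch for baseline 1, but none for baseline 0. A score already at the bottom of its scale cannot fall, so a woman who enters at grade 0 fails this component by construction. Because both components are required, she fails the primary endpoint.

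She is eligible, she stays in the analysis set, and the use of the better of the month 4 and month 6 responses does not rescue her, because the rule fails at both visits. A woman whose facial acne clears completely would be counted with the non-responders. This would understate the success rate in both arms and shrink the absolute difference that the trial is powered to detect.

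**Working it through.** **Step 1: list the outcomes.** Score 2 grades at follow-up that count as success, by baseline grade:

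| Baseline score 2 | Wording taken strictly | Read as grade 1 or lower |
|---|---|---|
| 0 | none | none |
| 1 | 0 | 0 |
| 2 | 1 | 0, 1 |
| 3 | 1 | 0, 1 |

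The empty row for baseline 0 is the same under both readings. The readings differ only for women who go from 2 or 3 to 0.

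**Step 2: can baseline 0 occur?** Entry needs GEA 2 to 4, at least 10 inflammatory lesions and no more than 3 nodules. Nothing there constrains score 2, and the two scores are graded independently. The Background section says that mandibular lesions are frequent in women, not that they are universal. So grade 0 is possible at entry. How often it occurs is not stated.

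**Step 3: reproduce the plan's sample size.** Inputs from Sample size {14}: 70% v 50%, type I error 5%, power 80%. Two-sided testing is from Statistical methods {20a}. Unpooled normal approximation:

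n = (1.960 + 0.842)² × (0.70×0.30 + 0.50×0.50) / 0.20² = 7.849 × 0.46 / 0.04 = 90.3, rounded up to 91 per group.

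This matches the stated figure. (The pooled formula gives 93.) Adding 9 per group gives about 100 per arm, or 200 in total.

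**Step 4: effect of forced failures.** Let q be the share of women at mandibular grade 0 at baseline, equal in both arms in expectation. Suppose 70% and 50% apply only to women who can succeed. The observed rates are then 0.70(1−q) and 0.50(1−q), and the difference is 0.20(1−q). With n per arm,

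power = Φ( difference / √(V/n) − 1.960 ), where V = p1(1−p1) + p2(1−p2).

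| q (assumed) | p1 v p2 | V | Power, 100 per arm | Power, 91 per arm |
|---|---|---|---|---|
| 0% | 70% v 50% | 0.4600 | 84% | 80% |
| 5% | 66.5% v 47.5% | 0.4722 | 79% | 75% |
| 10% | 63% v 45% | 0.4806 | 74% | 70% |

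Example for q = 10% at 100 per arm: 0.18 / √(0.4806/100) = 0.18 / 0.0693 = 2.597; 2.597 − 1.960 = 0.637; Φ(0.637) = 0.74.

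With the pooled formula at 100 per arm the three values are 82.8%, 77.9% and 72.7%, so the choice of formula does not change the picture.

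The column for 100 per arm is the more relevant one. Under the missing-data section {20c}, women lost to follow-up count as failures and are not removed, so the denominator stays near 100. Counting losses as failures also lowers both rates; that is a separate matter and is not modelled here.

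**The case against.** Four points can be made on the other side.

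1. **The number of such women may be small.** This stands. A reader might take the background's diffuse type, "the first is similar to teenager acne, with diffuse acne lesions over the face", as evidence of many women without mandibular acne. It is not: the same section places the mandibular location in the lower third of the face, so diffuse facial acne may well include it. Score 2 also covers a wide zone, down to the upper edge of the trunk. Shares of 20% or 30%, which would bring power at 91 per arm down to about 59% or 49%, have no support in the document.

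2. **The planning rates may already include these women.** This also stands. The sample size section gives 70% and 50% as success percentages per arm without restriction. If they describe all randomized women under this rule, there is no shortfall. The protocol does not say.

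3. **The dilution is conservative.** Correct: forced failures occur equally in expectation in both arms, so they neither favour spironolactone nor inflate the type I error.

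4. **Full clearance is not meant to be a failure.** A reader might infer from the strict wording that going from grade 2 or 3 to 0 counts as failure, and hence that the rule penalises the more effective arm. The document does not support this. The same section calls grade 0 no acne, accepts grade 0 as success from baseline 1, and treats 0 or 1 as the favourable mandibular state among the secondary endpoints. The clause evidently means grade 1 or lower. It needs clarification but is no evidence of bias between arms.

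None of this supplies the missing branch. An eligible woman at mandibular grade 0 remains a certain failure under the stated rule.

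**Conclusion.** Wrong as written. The primary definition requires a decrease on a scale whose lowest grade is admissible at entry, and neither the eligibility criteria nor the analysis set removes the women concerned. This is a defect in a rule that the protocol states in full, not a detail left to the analysis plan.

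The consequence is understated success rates and lost power, alike in both arms. The loss is conditional on two unknowns: the share at mandibular grade 0, and whether the planning rates already allow for it. If they do not, power at 100 per arm is still at least 79% up to a 5% share and about 74% at 10%; if they do, the planned sample size stands. The missing words or lower are a secondary wording fault that leaves the coding of full clearance open to two readings.

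The GEA clause for baseline grade 1 might look like a further fault, since entry requires GEA of at least 2. It affects no eligible woman and is harmless.

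**What to change.** By protocol amendment, before unblinding, define mandibular success by baseline grade:

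- baseline 2 or 3: grade 0 or 1;
- baseline 1: grade 0;
- baseline 0: remains at grade 0, so that success rests on the GEA component.

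Reword the opening condition to match, since a decrease in both scores is no longer required of every woman, and use the same derivation in the analysis program.

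No new data are needed, because both scores are already recorded at each visit. The cost is a dated protocol version and its submission to the regulator and the ethics board. The article states that recruitment was still under way, so at that time the change could be made without knowledge of results by arm.
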